### The Nested Process Evaluation

Research on using qualitative methods for feasibility RCT will be likely of particular value in refining understanding of how the intervention works and facilitating ongoing adaptation of intervention and evaluation design in preparation for a full trial (74). Thus, this study will nest a process evaluation, consisting of (A) qualitative interviews and (B) observations of the training sessions, with the aim to extend a more in-depth understanding of the acceptability and feasibility of PFA training intervention for this feasibility trial. First, individual interviews will be applied with trainees, as well as their clinical managers and trainers to reflect the perceived experience and impact of the PFA training, as well as barriers and facilitators to the training completion and program fit in. In particular, this study adds interview with participants' line managers from the clinical ward, whose role is to provide supervision of trainees practice after training completion, it is in consideration with lacking evidence in real practice from previous PFA training evaluation (29). Second, observations with trainees and trainers in the classroom will be used to expand the immediate response and feedbacks for the training, and to assess the level of intervention fidelity.

#### Sample

The process evaluation sample will use purposive sampling strategies in order to triangulate findings (75). Participants who will be invited to be interviewed include three different participant groups, including (1) trainees (*n* = 12) are those attending all the training sessions; (2) trainers (*n* = 4) who have been involved in this training; (3) clinical ward managers (*n* = 5) from PFA trainers' clinical ward. Maximum variation sampling will be considered via inviting trainees and managers representing diverse levels/types of training to participate and mangers in diverse working context to obtain rich understanding (76). Given the nature of the target qualitative sample participants, we expect this sample size will achieve data sufficiency.

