**Primary objectives: Feasibility**			
1-1 Recruitment and retention	• Can numbers of frontline healthcare workers be adequately recruited, trained, and retained for outcome analyses?	• Process outputs: trainees (number available in wards, number at training, number at supervision sessions; number completing measurement tools and time 1, 2 and 3)	Trainees
1-2 Adherence	• How many participants attend training sessions/supervision sessions? • What are the reasons for failing to attend training and supervision sessions?	• Attendance record for training and supervision sessions • Observation fieldnotes of training and supervision sessions • Qualitative interviews with expert trainers, and trainees	Trainees, trainers
1-3 Feasibility of measurement tools	• Are the assessment tools acceptable to participants for collecting training outcomes? • Are the measurement tools sensitive to assess the changes?	• Measurement tools completion rate, time for completion, number of missing items • Qualitative interview with participants about appropriateness of outcomes measures	Trainees
1-4 Overtime changes	• Do healthcare trainees' knowledge, attitudes, skills, well-being change after training, and is this sustained at follow up?	• Outcome's assessment pre-and post- training, plus 1- and 3-months follow-up • Calculation with mean score and standard deviation over time	Trainees

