#### Recruitment

Trainees who receive PFA training sessions and practice PFA after training completion in frontline will be sent an invitation for the interview via WeChat messages, and if they agree, their clinical manager will then be invited. The trainer of the PFA training intervention group will be invited to participate by the researcher prior to the start of the training and supervision sessions.

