#### Data Collection

##### Interviews

After written informed consent is obtained, qualitative interview with trainees will be conducted at 2 weeks after the training completion, while interview with trainers will be conducted after they have delivered the training and supervision. An indicated topic guide (see Table 3) is informed by the objectives of feasibility and acceptability which will guide the qualitative data collection. Interviews will take place on hospital premises, and the length of time taken range from 30 to 40 min.

**Table 3 T3:** Indicative topic guide after the PFA training completion.

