**Trainees**	
Acceptability and feasibility	How would you describe your experience of completing this training program? How do you value the PFA in your clinical practice? Any indicative changes in behaviors? How would you describe your experience of supporting your patients or colleagues through providing them PFA skills?
Satisfaction	How satisfied are you overall with training module? How clear do you find the concepts and ideas in the module?
Suggestions for further improvement	What do you think could be improved about? Is there anything missing?
Barriers	Are there any difficulties to taking part? What are the barriers to completing training course, and applying training to practice? What are the challenges to complete the assessment, with questions relating to reasons for not taking part/ discontinuation or dropping out?
Process of change	Are there any changes in your perspective of coping acute distress? If the answer is “Yes”, what are they?

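### Trainee interviews are restricted to those who attended all the training and then used PFA, although the protocol relies on them to explain non-attendance

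*Protocol article*

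**What the plan says.** In the protocol article, The Nested Process Evaluation, the Sample paragraph plans 12 trainee interviews and says that these trainees "are those attending all the training sessions". The Recruitment paragraph adds a second condition: "Trainees who receive PFA training sessions and practice PFA after training completion in frontline will be sent an invitation for the interview". Ward managers follow from the same group: "if they agree, their clinical manager will then be invited". On timing, the Interviews paragraph states that "qualitative interview with trainees will be conducted at 2 weeks after the training completion".

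Other parts of the article give the interviews work that needs a wider group:

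- Table 2, item 1-2 (Adherence, under the primary objectives) asks "What are the reasons for failing to attend training and supervision sessions", and its methods include "Qualitative interviews with expert trainers, and trainees", beside attendance records and fieldnotes.
- The opening of The Nested Process Evaluation says that interviews will cover barriers and facilitators to completing the training.
- Table 3, Trainees, Barriers asks about barriers to completing the course and to applying it, and about the challenge of completing the assessment, "with questions relating to reasons for not taking part/ discontinuation or dropping out".
- The Sample paragraph itself speaks of maximum variation sampling by "inviting trainees and managers representing diverse levels/types of training to participate".

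**The concern.** A question about why people miss sessions is put to a group chosen because they attended all the training. A question about barriers to using PFA is put to a group chosen because they used it. This is a stated eligibility rule that conflicts with the stated objective, so it is not a detail that a fuller protocol would be expected to supply.

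Two things are at stake. First, the adherence question loses its only first-hand trainee source on missed training. If completion turns out poor, the team would most need the accounts of those who left, and their reasons are hard to recover later. Second, what the trainee interviews say about acceptability comes from the people for whom the programme worked best, and the manager interviews carry the same selection.

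**Working it through.** The 12 interviews come without a formula or inputs, so there is no stated figure to reproduce. The check is a comparison of the texts, followed by an illustration of size.

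**Who is eligible**

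| PFA-arm trainee | Attended all training (Sample) | Practised PFA (Recruitment) | Can be interviewed |
|---|---|---|---|
| Attended all training, used PFA | yes | yes | yes |
| Attended all training, missed supervision only, used PFA | yes | yes | yes, on the wording |
| Attended all training, did not use PFA | yes | no | no |
| Missed part of training or withdrew from it | no | either | no |

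The last two rows are the people whom Table 2 item 1-2 (for training) and the Table 3 barrier prompts concern.

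The practice condition is also tight in time. Interviews fall 2 weeks after training completion, so an interviewee must have used PFA by about then. The Limitations section concedes that even the 3-month follow-up may be too short for trainees to apply what they learned.

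**Size, at the protocol's own threshold**

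Inputs:
- N = 80 (Sample Size) and 1:1 allocation (Randomization), so 80 / 2 = 40 in the PFA arm.
- Acceptable completion of all training sessions: 80% or more (Statistical Data Analysis), taken here to apply to the PFA arm.
- Trainee interviews: 12 (Sample).

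Non-completers possible with the criterion just met: 40 × (1 − 0.80) = 8. Number eligible for interview under the rule: 0.

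**What the restriction removes**

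Suppose, for illustration only, that the 12 were drawn at random from all 40. With m non-completers, the expected number interviewed is 12 × m / 40, and the chance of at least one is 1 − C(40 − m, 12) / C(40, 12).

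| Completion | m | Expected among 12 | Chance of at least one | Under the rule |
|---|---|---|---|---|
| 90% | 4 | 1.2 | 0.78 | 0 |
| 82% | 7 | 2.1 | 0.94 | 0 |
| 80% | 8 | 2.4 | 0.96 | 0 |
| 70% | 12 | 3.6 | 0.99 | 0 |

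At 82%, 40 × 0.18 = 7.2 is rounded to 7. Purposive sampling would not depend on chance, since it can fix the number directly. The document gives no figure for trainees who complete the training but do not use PFA, so that further exclusion cannot be sized.

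**The case against.** The best defence is that these interviews are not the only source.

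- **Non-attendance.** Item 1-2 also lists attendance records, fieldnotes and trainer interviews, and trainers face no completer condition. Managers are asked about difficulties in getting staff to take part. This stands to the extent that the trial would not be wholly ignorant of the reasons. But records give counts, and the other sources are second-hand on why someone stayed away.
- **Acceptability.** It also draws on trainers, managers, session recordings, and a follow-up questionnaire at 1 and 3 months that has no stated practice condition. This stands too: the selection affects the interview evidence, not everything said about acceptability.
- **Topic guide and sampling.** The discontinuation prompt is attached to completing the assessment, so a completer could answer part of it. Maximum variation is only to be considered, and some variation among full attenders remains possible. The prompt and the sampling statement are therefore supporting evidence. The firm conflict is with Table 2 item 1-2 and with the declared interest in barriers to completion.

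Some stronger readings are tempting but not supported:

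- **That nobody who missed any session can be interviewed.** The article distinguishes training from supervision sessions, and the Sample paragraph restricts only on training.
- **That the 20% loss to follow-up is shut out as well.** That allowance covers the whole study, with assessments to 3 months. Someone who trained, used PFA and was lost later is eligible at 2 weeks.
- **That the absence of control-arm interviews is a defect.** The process evaluation is aimed at the PFA training, and no Table 2 question asks about the acceptability of randomisation or of the comparator. Interviewing controls would be a preference.

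**Conclusion.** The inconsistency is real. The two conditions prevent the trial from hearing first-hand from PFA-arm trainees who missed training, withdrew from it, or did not use PFA, although a primary-objective question names trainee interviews as a source on non-attendance.

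The figure of 8 in 40 with none eligible assumes an even split of 80 and completion exactly at the 80% threshold. The favourable direction of the interview findings is a judgement from how the sample is selected, and its size cannot be computed from the document.

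This falls short of a critical flaw. The criteria in Statistical Data Analysis are quantitative, the Conclusions tie the main trial to 80% retention, and no progression rule uses the interviews. It should still be corrected before interviewing starts.

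**What to change.** In The Nested Process Evaluation, remove the full-attendance condition from Sample and the practice condition from Recruitment, so that both agree with Table 2 item 1-2 and Table 3. Keep 12 trainee interviews and reserve some of them purposively, for example 3 to 4, for PFA-arm trainees who missed training or supervision, withdrew, or did not use PFA. The 3 to 4 is a suggestion, not a derived number. Ask those who decline an interview for one brief reason by WeChat, which is already the invitation channel. Allow managers of these trainees to be invited on the same footing.

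The number of trainee interviews does not change. The costs are fewer completer interviews (8 to 9 of the 12), participants who are harder to reach, and a check on whether the wider invitation needs notifying under the two ethics approvals.

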#### Recruitment

Trainees who receive PFA training sessions and practice PFA after training completion in frontline will be sent an invitation for the interview via WeChat messages, and if they agree, their clinical manager will then be invited. The trainer of the PFA training intervention group will be invited to participate by the researcher prior to the start of the training and supervision sessions.

#### Data Collection

##### Interviews

After written informed consent is obtained, qualitative interview with trainees will be conducted at 2 weeks after the training completion, while interview with trainers will be conducted after they have delivered the training and supervision. An indicated topic guide (see Table 3) is informed by the objectives of feasibility and acceptability which will guide the qualitative data collection. Interviews will take place on hospital premises, and the length of time taken range from 30 to 40 min.

**Table 3 T3:** Indicative topic guide after the PFA training completion.

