**Secondary objectives: Acceptability**			
2-1 Program evaluation	• Did attending training and supervision lead to trainees' improvement in practice, if so, what were these? • What do trainees think about PFA training program and supervision sessions?	• Qualitative interviews with trainers, trainees, and clinical ward manager think about the PFA training (is the format acceptable, is there anything missing, likes and dislikes, barriers, and challenges to complete the training and supervision) • Observation fieldnotes from training and supervision sessions	• Trainer, trainees, clinical ward manager
• 2-2 Fidelity of training intervention	• Did the trainers deliver the training as intended?	• Analysis of observation fieldnotes and transcripts of training session video recordings. Researcher rated PFA training intervention using a fidelity assessment tool.	• Trainer

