### Intervention

#### Intervention

The whole process of this PFA training adaptation for delivery to Chinese frontline healthcare workers has been systematically described elsewhere. A detailed description of the Chinese ‘Preparing Me’ PFA training content has already been structured using the template for intervention description and replication checklist (TIDieR) in Table 1. Four trainers who have teaching and clinical psychological counseling background will be trained to deliver the PFA training intervention. Each of the six modules will be delivered in 75-min session blocks, incorporating didactic lectures, group exercises, role playing, and discussions to encourage active engagement and to improve the acquisition of PFA knowledge, skills, and techniques. All these sessions will be audio-recorded in preparation for the researchers to assess the fidelity using a PFA fidelity assessment tool. To support frontline healthcare participants to be able to apply the knowledge, skills, and techniques to their practice, two WeChat-based online supervision sessions will be offered.

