
### Data Collection

The schedule of enrolment, interventions, and assessments has been summarized in Figure 3. Demographic data will be recorded at baseline only, including age, gender, religion, marital status, living conditions, educational background, professional title, specialities, years of working experience, and experience of coping with crisis. Quantitative data will be collected from participants at three different times: baseline data will be collected before the PFA and psychoeducation training programmes (T0), the initial follow-up data will be collected immediately after training programmes are completion (T1), 1- and 3-months follow up data that will be followed up 1- and 3-months after the programmes are completed (T2, T3). The researcher will conduct data collection by providing each participant with a study pack at each time point. After presenting the information, the participants will be asked to complete these packs of assessment tools. To encourage participants' attendance at baseline and follow-up sessions, participants will be contacted by WeChat message at least 1 week before each data collection timepoint. The 1- and 3-months follow-up post-intervention measurement will be collected online via WeChat Wenjuanxing—a platform providing functions equivalent to Amazon Mechanical Turk. All questionnaires can be seen in Supplementary Materials.

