## Limitations

There are some limitations of this project. First, the design and evaluation of the feasibility trial has predominately focused on the outcomes associated with the frontline healthcare workers rather than the outcomes for recipients of PFA following a disaster, public health emergency, or other crisis. Second, the timeframe for follow up outcome measures is only 3 months, which may be insufficient time for PFA trainees to apply their knowledge and skills in practice evaluation.

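### The only trainee interview falls before T2 and T3, so it cannot explain missed follow-up or assess the follow-up questionnaire, although the plan gives it the measurement and drop-out questions

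*Protocol article*

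**What the plan says.** **Timing.** Under Interviews, in the nested process evaluation, "qualitative interview with trainees will be conducted at 2 weeks after the training completion". The same sentence says that "interview with trainers will be conducted after they have delivered the training and supervision". For the outcome assessments, the Data Collection section describes "1- and 3-months follow up data that will be followed up 1- and 3-months after the programmes are completed (T2, T3").

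**What the trainee interview is asked to deliver.**
- Table 2, item 1-3 (a primary feasibility item), lists: "Qualitative interview with participants about appropriateness of outcomes measures".
- Table 3, Trainees, Barriers, asks: "What are the challenges to complete the assessment, with questions relating to reasons for not taking part/ discontinuation or dropping out".
- Table 2, item 2-1, asks: "Did attending training and supervision lead to trainees' improvement in practice, if so, what were these". It also asks for trainees' views of the supervision sessions.

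**Who is interviewed.** The Sample section names 12 trainees who attended every session. The Recruitment section of the process evaluation limits invitations to those who have received the PFA training and have since used it at work.

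**What comes after the interview.** The Secondary Objectives section places the 11-item PFA Training Follow-up Questionnaire at 1 and 3 months only. Data Collection moves the T2 and T3 assessments to an online platform. On supervision, the Intervention section says that "two WeChat-based online supervision sessions will be offered"; the visible text gives no dates.

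**The concern.** A question about why people miss assessments or leave can only be answered once those events have had a chance to happen. At 2 weeks the trainees know the baseline and immediate post-training packs and nothing later. The part of the trial where loss to follow-up and missing data are most in doubt is still ahead of them.

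Retention carries the decision. The Conclusions section makes 80% retention the condition for a main trial, Statistical Data Analysis requires less than 20% missing data at each time point, and Sample Size allows for 20% loss. Item 1-1 of Table 2 records retention by counts alone, and the trainer and manager guides in Table 3 have no question on completing assessments or dropping out. If retention falls short, the trial will report how many were lost, but the one interview that asks why will have been held too early.

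**Working it through.** **1. The plan's own figure.** Sample Size gives 80 recruited for at least 64 completers with 20% loss. 64 / (1 − 0.20) = 80, which reproduces the stated number. The plan thus allows for 80 − 64 = 16 losses. It does not say how many would occur after T1.

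**2. Dates.** Take a month as 365.25 / 12 = 30.4 days and count the interview, T2 and T3 from the same day.

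| Event | Day | Interview precedes it by | Interview day as share of the interval |
|---|---|---|---|
| Trainee interview | 14 | – | – |
| T2 | 30.4 | 30.4 − 14 = 16.4 days | 14 / 30.4 = 46% |
| T3 | 91.3 | 91.3 − 14 = 77.3 days | 14 / 91.3 = 15% |

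Two of the four assessments (T0, T1) precede the interview and two follow it.

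**3. Does the choice of day zero matter?** If both clocks start at the course day, or both at the end of supervision, the gaps are those above. If the interview is counted from the course day and T2/T3 from the end of supervision, the gaps are wider. The order reverses only if the interview is counted from the end of supervision while T2/T3 are counted from the course day. Supervision would then have to end more than 16 days after the course to put T2 first, and more than 77 days after it to put T3 first. The text does not suggest this mixture: the Follow-up Questionnaire and the trainee interview are both dated from the training.

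**4. Each assigned question against what a trainee knows at day 14.**

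| Question | Available at 2 weeks | Not available |
|---|---|---|
| Appropriateness of measures (item 1-3) | Burden and relevance of the T0 and T1 packs | Follow-up Questionnaire; online T2/T3 delivery |
| Assessment and drop-out (Table 3) | Difficulties up to T1 | Reasons for missing T2 or T3 |
| Practice change (item 2-1) | Early change, since invitees must already have used PFA | Sustained change; any effect of supervision held later |
| Views on supervision (item 2-1) | Depends on dates that are not visible | Depends on dates that are not visible |

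**5. Extra contact in one arm.** Only PFA trainees are invited. With 1:1 allocation of 80, that is 12 / 40 = 30% of the arm, each interviewed for 30 to 40 minutes before T2 and T3 self-report. The documents give no basis for estimating an effect.

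**The case against.** Several points on the other side stand.

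- **Practice change.** A reader might infer that the interviews cannot address it at all, or that the trial's evidence on practice rests on 2 weeks. The documents do not support that. Interviewees must already have used PFA. Table 2 also names trainer interviews (after supervision), manager interviews (no date given) and fieldnotes. The Follow-up Questionnaire measures application at 1 and 3 months, and trainers keep field notes during supervision. The authors' own remark about 3 months, "which may be insufficient time for PFA trainees to apply their knowledge and skills in practice evaluation", concerns the outcome follow-up; it suggests that 2 weeks is early, but says nothing directly about the interviews.
- **Supervision.** A reader might infer that trainees are interviewed before supervision. The contrast with the trainer interviews hints at it, but Table 1 lists the supervision sessions under its training-session column, both could fall within 2 weeks, and the schedule in Figure 3 is not available here. The order is not established, and a missing figure is no error in the plan.
- **Prompting.** A reader might infer that the interview biases the PFA arm's later self-reports. That is plausible but unquantified. The interview is prespecified, supervision already involves planned reflection on practice, and the trial tests no effectiveness hypothesis.
- **Drop-out.** Table 2 does not itself assign reasons for T2/T3 loss to interviews; the wording is one prompt in an indicative guide, and it does not name T2 or T3. Trainees who completed T0 and T1 can also judge those measures.
- **Trade-off.** Much of the trainee guide concerns the course itself, which is best recalled early.

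None of this changes the order of events. No other interview guide in the article covers reasons for missed assessments, and no interviewee will have used the Follow-up Questionnaire.

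**Conclusion.** The point holds in a limited form. The trainee interview, about 16 days before T2 and 77 days before T3, cannot inform reasons for T2/T3 non-completion, or the suitability of the Follow-up Questionnaire and the online follow-up. The article nevertheless assigns the measures and drop-out to it. For practice, it captures early change only. For supervision, the order needs stating.

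This rests on counting the interview and the follow-up from one day, or the interview from the earlier one, and on no later trainee interview existing. No numerical bias is claimed. The 46% and 15% only locate the interview within the follow-up period.

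**What to change.** Amend the Interviews section so that the topics on measurement, drop-out, supervision and sustained practice are asked after each trainee's T3 assessment. If early reactions to the course matter, keep a short contact at 2 weeks limited to that. State the supervision dates relative to both contacts. Holding the reflective topics until after T3 also avoids an extra prompt in the PFA arm before the T2 and T3 self-reports.

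The cost is a change to the schedule wording, plus either weaker recall of the course day at 3 months or one brief extra contact. Qualitative fieldwork ends later.

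The change has a limit. Interviewees are trainees who attended every session, so a later interview can reach attenders who missed T2 or T3 but will not fully explain why others stopped training. The Table 3 prompt should be worded accordingly unless the sample is widened.
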